# Voluntary Saccade Training Protocol in Persons With Parkinson’s Disease and Healthy Adults

**DOI:** 10.3389/fnagi.2019.00077

**Published:** 2019-04-05

**Keywords:** eye movements, saccades, Parkinson’s disease, training, voluntary saccades, healthy adults, saccade latency, saccade amplitude

## Abstract

**Background:** Voluntary saccade function gradually decreases during both the progression of Parkinson’s disease (PD) and neurologically healthy adult aging. Voluntary saccades display decreased length and increased saccade latency, duration, and the number of compensatory saccades in aging and PD. Saccades serve as the key eye movement for maintaining salient features of the visual environment on the high visual acuity fovea of the retina. Abnormal saccade behavior has been associated with freezing of gait in PD. We have not identified any studies that have investigated improvement in voluntary saccade function using voluntary saccade training.

**Objective:** We report an experimental protocol that tests a training paradigm following the principle of specificity to improve voluntary saccade velocity and amplitude, while decreasing latency and the number of compensatory saccades.

**Methods:** Persons with PD (n = 22) and persons with no known neurological disorders (n = 22) between the ages of 40 and 65 years will be recruited. In a randomized-block study design, all participants will perform voluntary saccades to targets in eight cardinal and intercardinal directions. In each of the eight sessions during the four-week intervention period, participants will train at three target amplitudes. Participants will perform 40 trials for each amplitude block, consisting of five randomly presented repetitions for each direction. Voluntary and reflexive saccades will be recorded pre- and post-intervention, along with clinical mobility assessment using the Movement Disorder Society Unified Parkinson’s Disease Rating Scale. Mobility scores, the amplitude, latency, and duration of the first saccade, and the number of saccades to reach the fixation target will be analyzed using an ANOVA of mixed effects.

**Discussion:** This protocol holds promise as a potential method to improve voluntary saccade function in persons with PD. Should persons with PD not improve on any outcome following the intervention, this lack of response may support the use of saccade assessment as a response biomarker for the diagnosis of PD.

**Trial Registration:** This protocol was retrospectively registered at ISRCTN (ISRCTN.com) since July 25, 2018. The first participant was recruited March 12, 2016. The protocol identifier is 17784042.

**Descriptive Title:** A two-arm, pre/post-protocol to compare the effects of a four-week voluntary saccade training intervention in persons with Parkinson’s disease and healthy adults aged forty years or older.

## Introduction

### Voluntary Saccade Function Impairment in Parkinson’s and Healthy Aging Adults

Visual function is a major area of decline in Parkinson’s disease (PD) progression and healthy aging adults (Terao et al., 2011; Dowiasch et al., 2015). One element of visual function that has been correlated with PD progression and neurologically healthy aging by a number of studies is saccade behavior (Terao et al., 2011; Dowiasch et al., 2015; Seferlis et al., 2015; Noiret et al., 2017). Saccades are the ballistic eye movements that allow the high acuity fovea of the retina to quickly orient toward salient elements of the visual environment. Persons with PD exhibit lower saccade amplitude, higher saccadic latencies, and longer durations to achieve targets (Mosimann et al., 2005; Terao et al., 2011). Deficits in voluntary saccade control contribute to mobility impairments related to turning during navigation (Ambati et al., 2016; Nemanich and Earhart, 2016). It has been noted that turning during navigation in persons with PD increases instability and risk of falling (Stack and Ashburn, 1999). Voluntary saccade function deficits are also present to a lesser extent in neurologically healthy aging adults (Chen and Machado, 2016; Fernandez-Ruiz et al., 2017).

### Existing Treatments

Various treatments, including electrical brain stimulation, have been suggested for improving voluntary saccade function in PD (Chen and Machado, 2016). An eye-movement training protocol consisting of horizontal saccades to increasingly distant points and cognitively more challenging targets, such as letters and words, was shown to increase reading speed in older adults with age-related macular degeneration (Seiple et al., 2005). Other treatments include the anti-saccade paradigm, which requires the suppression of a saccade to a stimulus and voluntary saccade to a location of equal eccentricity in the opposite direction (Jamadar et al., 2015). However, such studies focus on accuracy and error rate and do not address hypometria as is needed for navigation (Jamadar et al., 2015; Ambati et al., 2016).

### Need for a Trial

Recent work has investigated the difference between smooth-pursuit performance in persons with PD and persons with no known neurological disorders (Ito et al., 2013; Fukushima et al., 2015). However, the current literature does not include voluntary saccade practice as a method of comparing potential improvements in voluntary saccade function for persons with PD and healthy aging adults. While we cannot predict if there will be immediate short- or long-term benefits to the participants in the study, exercising eye movements can potentially benefit eye movement control. As with any other movement training, exercise increases circulation to the muscles and improves their physiological function. Physical mobility is of the utmost importance for the quality of life in the general population. Furthermore, recent PD literature indicates that abnormal saccade behavior is associated with the freezing of gait and difficulty in navigation (Lohnes and Earhart, 2011; Ambati et al., 2016; Nemanich and Earhart, 2016; Stuart et al., 2017). Improving abnormal saccade behavior may affect freezing of gait and other motor-related PD symptoms. Improving these outcomes for persons with PD has the potential to improve the same daily activities as those in healthy aging persons, as well as increasing walking ability (Lohnes and Earhart, 2011; Stuart et al., 2017). Further, saccade function has been demonstrated as a key factor in the slowing of reading, decrease in driving abilities, and eye-hand coordination in several studies (Schmitt et al., 2015; Coats et al., 2016).

#### Saccade Biomarker Potential

Identifying non-invasive biomarkers of PD onset is imperative for disease treatment. Saccadic abnormalities have been suggested as a diagnostic tool for PD, including early stage progression marking and differential diagnosis from other tremor disorders such as essential tremor (Yerram et al., 2013). Saccade abnormalities may also be useful as markers for frontal cortex and basal ganglia malfunction and degeneration in PD, as well as changes in the cerebellum (Terao et al., 2013). van Stockum et al. (2012) later suggested that due to the differences in reports of saccadic latency deficiencies and facilitation, the hypometria seen across different saccadic paradigms may be a better measure for the effect of PD on saccades. Control of voluntary saccades has also been highlighted as a promising area of motor control in general (Baird-Gunning and Lueck, 2018). Diagnosis in the early stages will benefit individuals with PD, enabling prompt disease treatment and management to slow disease progression. In addition to the person diagnosed with PD, this also benefits their immediate family and support network.

One criticism against saccade measurements as a diagnostic tool for PD is that the abnormalities seen in saccadic movements tend to differ based on the experimental context (MacAskill and Anderson, 2016). Abnormalities in saccade latency and amplitude are known to occur in multiple neurodegenerative disorders, which could lessen biomarker specificity (MacAskill and Anderson, 2016). However, recent reviews outlined differential characteristics of saccadic performance in PD and several other neurodegenerative diseases (Termsarasab et al., 2015; MacAskill and Anderson, 2016). Additionally, research into the characteristic relationship between saccade duration, peak velocity, and amplitude has not been extensively undertaken in PD. This “main sequence” is believed to characteristically optimize the costs of speed and saccadic accuracy at a given amplitude (Bahill et al., 1975; Harris and Wolpert, 2006). If the main sequence relationship is affected by training differences in persons with PD compared to neurologically healthy persons, the biomarker potential for voluntary saccade training response would be further supported. One benefit of saccadic measurements as a PD biomarker is that assessments of eye tracking systems are non-invasive, unlike biochemical markers, which require blood or CSF extraction. Additionally, saccade testing could occur in a clinical setting without the need for physician supervision and biochemical testing facilities, with the most common side effect being possible fatigue from eye movement.

#### Risks/Benefits Comparison

Risks associated with eye training include the possibility of eye strain and orbital myositis, which is a rare autoimmune disorder that may result from inflammation due to vigorous exercise. These risks are minimal and reduced by the progressive periodization of amplitudes in the training regimen. The potential benefits of improved eye coordination, range of motion, and responsivity to visual stimuli outweigh the minimal risk for eye strain/injury. The greatest amount of risk in the study is associated with performing OFF-state assessments in participants with PD. The OFF-state occurs when the motor effects of levodopa and other dopaminergic medications are not present due to delayed intake of these medications. During the OFF-state, intensified motor symptoms that may be uncomfortable – such as dyskinesia, rigidity, spasticity, bradykinesia, dystonia, and freezing – may be present. However, discomfort and possible risk of falls are mitigated by limiting the inclusion criteria to only include individuals in the early stage of the disease (H&Y score 1–2; see Table 1 for criteria) where these symptoms are not severe in general or in the OFF-state. Neurologist clearance – as well as facilitation of dialogue between participant and neurologist, participant and researchers, and researchers and neurologists – will provide an informed environment for how to manage the two-hour disruption in medication. Further, risks of discomfort and falling will be minimized through the use of wheel chairs, gait belts, and secure seating during the eye-tracking assessment.

**Table 1 T1:** Criteria for Hoehn & Yahr stages one and two.

H&Y: Stage One	H&Y: Stage Two
1. Signs and symptoms on one side only	1. Symptoms are bilateral
2. Symptoms are mild	2. Minimal disability
3. Symptoms are inconvenient but not disabling	3. Posture and gait affected
4. Usually presents with tremor of one limb	
5. Friends have noticed changes in posture, locomotion, and facial expression	

It is common practice to perform assessments in the OFF-state in the field of PD clinical research because the methodology provides a controlled environment for assessing the disease without the influence of movement-modifying medications that mask the disease condition. This is especially important in biomarker research of PD patients. Assessment in the OFF-state condition increases relevance and generalizability of the study evidence to populations with undiagnosed and untreated PD. Generalizability of results may lead to greater instances of early detection and allow for informed diagnoses of individuals not yet receiving movement-modifying medications. The increased applicability of data collected in OFF-state assessments far outweighs the risks.

### Saccade Training Time Selection

Due to the current lack of literature studying voluntary saccade training through practice, the training dose of 30 min, twice per week, for four weeks was chosen based on training doses seen in other eye training protocols (Fischer and Hartnegg, 2000; Bibi and Edelman, 2009; Jamadar et al., 2015; Knox and Wolohan, 2015; Kleiser et al., 2017; Johannesson et al., 2018). The limit of 30 min of practice per day was chosen to reduce the likelihood of eye strain.

### Explanation for Choice of Comparators

There will be no comparator intervention used in this study. The effects of the voluntary saccade training intervention in persons with PD will be compared to those in persons with no known neurological disorders so that we can determine whether the group with PD is more responsive to the intervention. A greater response in the participants with PD would indicate a significant improvement in saccade performance. A lack of response to the intervention would indicate a resistance to improvement in saccade performance that may be characteristic of persons with PD.

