##### Secondary objectives

To determine whether training voluntary saccades affects motor disability in persons with PD. We will also investigate whether training voluntary saccades affects the relationship of the main sequence. Should statistical analysis reveal that these improvements are absent in participants with PD, we propose that saccade performance would be a potential early PD biomarker.

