#### Sample Size

There will be two groups with the same treatment: (1) a control group of participants with no known neurological disorders and (2) a test group comprised of participants with PD that have H&Y levels 1–2. In the absence of existing data in the literature to estimate the required same sample size for a protocol of this nature, the estimation is based on the number of eyes tested and trained in other eye movement studies and a 10% attrition rate seen in other studies performed by the authors (Hall et al., 2010; Knox and Wolohan, 2015; Ivanov et al., 2016; Heath et al., 2017).

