The superior colliculus (SC) has been identified as a key area for target and timing selection for saccades in primates (Port and Wurtz, 2009). Neurons in the SC are thought to form a map of saccades by direction and amplitude, requiring the activity of a group of SC neurons to form a saccade of the correct amplitude and direction (Sparks, 2002). SC neurons receive cortical and subcortical input and communicate output to the midbrain and pontine areas, as well as all premotor areas associated with control of eye and head movements (Sparks, 2002). The cortical frontal eye fields – while not necessary for saccade initiation – contribute to saccade control, through activity mediated by the SC (Sparks, 2002). The cerebellum plays a key role by creating the error signal for saccades, which contributes to saccade accuracy, speed, and lack of variability (Robinson and Fuchs, 2001). This signal is also generated by different areas of the cerebellum depending on whether the saccade has a horizontal or vertical direction (Robinson and Fuchs, 2001). The posterior vermis and caudal fastigial nucleus generate horizontal saccade signals, while vertical saccade information is handled by the interpositus nucleus (Robinson and Fuchs, 2001). Through these signals, the cerebellum adds correction information to saccade commands prior to initiation of movement to achieve accurate saccades of the necessary speed (Robinson and Fuchs, 2001).

A lack of response to voluntary saccade training in the primary or secondary outcome measures would support the use of this protocol for testing saccades as part of a biomarker assessment for early detection and diagnosis of PD. An added dimension of biomarker potential may come from a differential response of the main sequence to the training between the two groups as measured by changes in characteristic peak velocity for given saccadic amplitudes. This would create a more robust saccade-based biomarker by adding a treatment-response dimension to the characterization suggested as a diagnostic tool by previous studies (Terao et al., 2013; Yerram et al., 2013; Termsarasab et al., 2015).

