## Conclusion

This intervention holds significant promise as a low-cost, low resource-demand tool to improve motor functions of the eyes in persons with PD and adults with no known neurological disorders as well as mobility outcomes associated with eye function in persons with PD. Should persons with PD not show improvements on any metric following the intervention, a lack of response to voluntary saccade training may support saccade assessment as a biomarker for early detection and diagnosis of PD.

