Inclusion criteria: For participants with PD: (1) medically stable with diagnosis of PD by meeting the United Kingdom PD Society Brain Bank Criteria, (2) to have a Modified Hoehn & Yahr stage 1–2 (with unilateral involvement only, unilateral and axial involvement, and bilateral involvement without impairment of balance) in the conventionally defined OFF medication state, (3) to have medical clearance form from their physician for participation in the study, (4) to be in a stable regimen of PD medication 30 days prior to the initiation of the study and until the completion of the study, (5) to be willing and able to provide informed consent, (6) to be of age 40 and up, and (7) must have a caregiver/family member present for OFF-state assessment sessions.
For neurologically healthy participants: (1) no known neuromuscular disorders, (2) to have medical clearance form from their physician for participation in the study, (3) to be willing and able to provide informed consent, and 4) to be of age 40 and up.
Exclusion criteria: (1) presence of dementia based on The Montreal Cognitive Assessment (MOCA) –score of less than 25, (2) diagnosis of comorbid neurological disorder such as epilepsy, (3) history of neurological injury such as stroke, (4) history of brain surgery such as deep brain stimulation, (5) concurrent severe medical illness which in the opinion of the research team will preclude participation in the study (such illnesses may include but not limited to severe or uncontrolled cardiovascular disease, hypertension, pulmonary disease, or diabetes), (6) inability to attend and participate in at least seven of the training sessions, (7) uncorrected vision, history of retinal disease (e.g., macular degeneration), presence of optic neuropathy due to glaucoma or ischemic optic neuropathy, pseudoexfoliation syndrome, ocular surgery, ocular trauma, visually significant cataract, orbital myositis, blindness or refractive errors outside –5 to +3 D, (8) indication by the participant’s neurologist in the medical release form that testing the participant in the OFF-medication state would put PD participants at significant risk for medical complications.
Study type: Interventional
Allocation: no randomization; Intervention model: two-arm pre-post; Masking: non-masked
Primary purpose: eye movement training
Study Phase: Phase 0
Date of first enrolment: March 12, 2016
Target sample size: 44
Recruitment status: Recruiting

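### No response in PD is read as PD resistance and biomarker support, and a larger PD than control change as improvement; the design supports neither inference

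*Protocol article*

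**What the plan says.** Explanation for Choice of Comparators states that "There will be no comparator intervention used in this study" and then says how two results will be read:

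- A larger change in PD than in controls: "A greater response in the participants with PD would indicate a significant improvement in saccade performance".
- No change in PD: "A lack of response to the intervention would indicate a resistance to improvement in saccade performance that may be characteristic of persons with PD".

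The second reading recurs. Secondary objectives ties it to the analysis: "Should statistical analysis reveal that these improvements are absent in participants with PD, we propose that saccade performance would be a potential early PD biomarker". The Discussion says: "A lack of response to voluntary saccade training in the primary or secondary outcome measures would support the use of this protocol", and goes on to early detection and diagnosis. The Conclusion says that "a lack of response to voluntary saccade training may support saccade assessment as a biomarker for early detection and diagnosis of PD", on condition that PD participants fail to improve on every metric. The Abstract has a similar condition.

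On the design, Sample Size says "There will be two groups with the same treatment", and the registration table under Research Ethics Approval gives "Allocation: no randomization; Intervention model: two-arm pre-post; Masking: non-masked". The size of 22 per group rests on the number of eyes studied elsewhere and on 10% attrition. Statistical Methods names four variables for each of two saccade types, which makes eight.

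**The concern.** **Null result.** Failure to find a change is not evidence that there was none, unless the estimate is precise enough to exclude a change that matters. The article gives no margin or CI criterion for lack of response. It also never makes the PD-specific reading depend on the controls having responded. If neither group changes, nothing specific to PD has been seen, yet the text would still count the result towards a PD biomarker.

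**Group difference.** The healthy group is trained too, so it controls for diagnosis and not for training. A larger change in PD can arise because PD improved, because controls got worse, or because retest gains differ. Voluntary testing uses the training task (Saccade Function Testing), so retest practice is part of every change score.

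At stake is the published conclusion. An imprecise null could be reported as support for diagnosing PD, and a group contrast as evidence of improvement.

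**Working it through.** **Inputs from the article.** 22 per group and 10% attrition (Recruitment, Sample Size); eight primary variables (Statistical Methods); no alpha, power, effect size, SD or margin. There is therefore no power figure to reproduce.

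**Assumptions.** Two-sided 5%; effects in SDs of the change score; true effects of 0.3, 0.5 and 0.8 SD as a range; correlation between outcomes of 0 to 0.8.

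**1. Completers.** 22 × 0.9 = 19.8, about 20 per group.

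**2. Precision.**
- Within PD: t(0.975; 19)/√20 = 2.093/4.472 = 0.47 SD.
- Between groups: t(0.975; 38) × √(2/20) = 2.024 × 0.316 = 0.64 SD.

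An observed PD change of exactly zero is thus compatible with a true gain of almost 0.5 SD.

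**3. Missed PD gain, one outcome** (noncentral t, 19 df, noncentrality d√20).

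| True PD gain | Noncentrality | Power | Missed |
|---|---|---|---|
| 0.3 SD | 1.34 | 25% | 75% |
| 0.5 SD | 2.24 | 56% | 44% |

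**4. Missed PD gain on the strict reading** (no significant improvement on any of eight outcomes, with the same true gain on all eight; simulated).

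| Correlation | 0.3 SD | 0.5 SD |
|---|---|---|
| 0 | 10% | 0.1% |
| 0.3 | 24–25% | 3% |
| 0.5 | 34% | 7% |
| 0.8 | 51% | 18–19% |

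With independent outcomes this is simple arithmetic: 0.754⁸ = 0.10 and 0.436⁸ = 0.001.

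**5. PD change larger than control change, read as improvement** (two-sample t, 20 per group, noncentrality d√10).
- PD truly unchanged, controls worsen by 0.8 SD: noncentrality 2.53, and the contrast favours PD significantly in 69% of trials. In 24% of all trials it does so while the observed mean PD change is zero or negative.
- PD unchanged, controls worsen by 0.3 or 0.5 SD: 15% or 34%. The same figures apply to any difference of that size that is not due to training.
- Both groups truly improve by 0.8 SD: the contrast favours PD in only about 2.5% of trials, although a test of PD's own change has 92% power.

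So the contrast can signal without PD improvement and stay silent when PD improves.

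**The case against.** Several points on the other side are sound.

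- **These are statements of interpretation, partly hedged.** The text speaks of what may be characteristic, what may support and what is potential. A reader might infer formal decision rules, or claims of proof; the article contains neither. Reading lack of response as a non-significant test is also an inference, drawn from the reference to statistical analysis in Secondary objectives and the absence of any other criterion. The hedging is not uniform, however: the comparator section and the Discussion say what a result would indicate or would support.
- **The Abstract and Conclusion require failure on every outcome.** Eight outcomes then make the null reading harder to reach, and the 44% single-outcome figure does not apply there. Step 4 does, and at 0.3 SD the error is still material.
- **It is a declared pilot** (Trial Design, Modifications). A size without a power basis is not an error in a pilot. It does leave less room for conclusions from a null.
- **The absence of an untrained group is disclosed.** That is so, but the sentences that follow do not respect it.

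Three stronger readings should be resisted. Controls might be thought to sit at ceiling, but the article gives no control values; the Introduction says only that their deficits are smaller. One might quote the 34% chance of any significant result among eight independent tests (1 − 0.95⁸), but that counts worsening as well, and multiplicity handling may be in an analysis plan that is not shown. One might also say that almost any result supports a claim, but equal improvement in both groups, or a smaller improvement in PD, meets neither sentence.

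**Conclusion.** The point holds as an error of inference. The two sentences on comparators, and the statements in the Abstract, Secondary objectives, Discussion and Conclusion that carry the null reading on, state conclusions that this design cannot support.

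The size of the null problem depends on the reading: 75% or 44% of real gains of 0.3 or 0.5 SD missed on one outcome, against about 10–51% or 0.1–19% if all eight must fail. The group-difference problem does not depend on sample size, because no number of trained controls separates training from retest. The percentages rest on assumed alpha, effect sizes and correlations; only the group size and the attrition rate come from the article.

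Even a well-established non-response in PD would be a difference between groups. It would not show diagnostic accuracy.

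**What to change.** Replace the two interpretive sentences in Explanation for Choice of Comparators and align the Abstract, Secondary objectives, Discussion and Conclusion:

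- **Improvement in PD.** State it only when the 95% CI of PD's own change lies wholly in the direction of improvement: a decrease for latency and saccade count, an increase for amplitude and velocity, as in Research Hypothesis. Call it pre-post change (training plus retest). Call the group-by-time contrast differential change.
- **PD-specific non-response.** State it only when the group-by-time CI shows that controls improved more, and the CI limit of the PD change on the improvement side excludes a margin fixed before analysis. Otherwise report the result as inconclusive.
- **Biomarker wording.** Do not conclude early detection or diagnosis from a null result. Present it at most as a hypothesis for a later study.

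A single primary variable or a particular multiplicity procedure is not needed for this correction.

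**Cost.** No extra participants or data. The claims become weaker, and a margin must be chosen and justified before analysis. At 20 completers, an observed PD change of zero excludes only margins above about 0.47 SD, so inconclusive will be a common and honest result.
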